### Primary outcomes

#### Recruitment/retention rates

Recruitment (the proportion of those approached to those who agree to participate; target >65%) and retention (the proportion of those who qualify to those who complete the study; target >80%) will be used as evidence to determine feasibility and acceptability of TEACH.

Qualitative data on TEACH feasibility/acceptability will also be gathered post-treatment by a trained graduate student of psychology. A semi-structured qualitative interview (~30 minutes) will be conducted with participants to assess feasibility and acceptability of the protocol.

### Secondary outcomes

#### Fatigue

Fatigue in the past seven days will be measured via the *PROMIS Pediatric Fatigue Short Form* or *Adult Short Form* [20, 21]. Adolescent participants will complete the pediatric short form which includes 10 items scored on a 5-point Likert scale (*0* = *never, 4* = *almost always*) to generate a score 0–40, with higher scores indicating more fatigue. Young adult participants will complete the adult short from that consists of eight items scored on a 5-point Likert scale (*1* = *not at all, 5* = *very much*) to create score 8–40, which are converted into T-scores. T-scores ≥ 60 are eligible.

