#### Depressive symptoms

*The Children’s Depression Inventory 2nd Edition (CDI-II)* and *The Beck Depression Inventory-II (BDI-II)* assess depressive symptoms in the past two weeks for children and adults, respectively [22, 23]. The CDI-II consists of 28 items scored 0–2 for a total score 0–56. The BDI-II is a 21-item measure (scores 0–3) for a score 0–63, which can be transformed into a T-score. Higher scores on these measures indicate more severe symptoms. T-scores of ≥ 60 and ≤ 90 indicate eligibility.

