### Statistical analysis plan

Recruitment/retention rates and qualitative analysis of the semi-structured interview will assess feasibility, tolerability, and acceptability of TEACH. Evidence of feasibility is demonstrated by > 65% of patients/families approached will agree to participate (H1) and > 80% of recruits will complete the TEACH protocol (H2). Participant feedback about TEACH will be solicited and will support program feasibility (H3). Recorded qualitative interviews will be transcribed for the team to identify and code themes and key content domains. Discrepancies between reviewers will be discussed at length until a consensus is reached. Members of the research team ([name], [name]) are experts in qualitative data analysis [18, 44–48].

A repeated measures ANOVA will evaluate the hypotheses outlined in Aim 2. Participants will be allocated to the TEACH + TAU or TAU group. The mean change in fatigue (main secondary outcome), depressive symptoms, and pain from baseline to eight-week post will be analyzed separately to determine the effect of TEACH on these symptoms in comparison to the control group.

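### Fatigue and depression are scored on different scales below and above 18, and the plan names no common metric for the single mean change it analyses per symptom

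*Protocol article*

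**What the plan says.** All of this is in the Protocol article.

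- **Fatigue.** Adolescents complete a 10-item form scored "to generate a score 0–40, with higher scores indicating more fatigue". Young adults complete an 8-item form scored "to create score 8–40, which are converted into T-scores". The entry rule, "T-scores ≥ 60 are eligible", has no age limit.
- **Depressive symptoms.** "The CDI-II consists of 28 items scored 0–2 for a total score 0–56". The BDI-II, for adults, is summed "for a score 0–63, which can be transformed into a T-score". The entry rule, "T-scores of ≥ 60 and ≤ 90 indicate eligibility", is likewise not tied to one inventory. The Eligibility criteria section also states the depression exclusion in T-scores.
- **Statistical analysis plan.** A repeated measures ANOVA is used: "The mean change in fatigue (main secondary outcome), depressive symptoms, and pain from baseline to eight-week post will be analyzed separately". The separation is between symptoms, not between age groups, and no age term is named.
- **Sample Size Estimate.** One fatigue comparison, 30 versus 30, effect size 0.6, two-sided 5% level, 76% power, for an averaged difference between two group means.
- **Randomization and blinding.** Age group (under 18, 18 and over) is a stratification factor.

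Pain uses one 0–10 scale at every age and is not affected.

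**The concern.** The article does describe scoring, but unevenly: one fatigue form is carried through to T-scores and the other stops at a raw total. Someone who follows the scoring text and then the analysis text to the letter would average raw points from adolescents with T-score points from adults.

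Two things would follow. The estimate would have no single unit, which matters because the trial sets out to estimate the effect on fatigue, its main secondary outcome and the basis of the sample size. And each age group would count in proportion to the spread of its scale as well as its number of participants. Whether power also suffers depends on whether the contrast uses change within a person or levels between persons.

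**Working it through.** **Inputs from the article:** 30 per arm, effect size d = 0.6, two-sided 5% level, stated power 76%, 80% retention, 75 enrolled, fatigue ranges 0–40 (adolescent, raw) and 8–40 (adult, before conversion).

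**Assumed, because the article gives no figures:** correlation between occasions ρ = 0.5; adult T-score SD 10; adolescent raw SD equal to k times the adult SD, with k from 0.5 to 1.0; adults 30–50% of the sample; a true effect of 0.6 SD in each age group.

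**1. The plan's own figure.** For an average over two occasions the SD factor is √((1+ρ)/2) = √0.75 = 0.866.
- z = (0.6/0.866) × √(30/2) − 1.96 = 0.693 × 3.873 − 1.96 = 0.72, so power is 76.5% (75.1% by noncentral t). This agrees with the stated 76%.
- Enrolment: 60/0.80 = 75, which also agrees.

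Reproduced this way, the 76% is one comparison of all 60 completers with a single effect size. It presupposes one scale, and the text does not define one.

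**2. Unit and weight.** Let q be the adolescent share. Their share of the pooled effect is qk / (qk + 1 − q).
- q = 0.5, k = 0.5: 0.25/0.75 = 33%.
- q = 0.5, k = 0.8: 0.40/0.90 = 44%.
- As an illustration, with an adolescent raw SD of 8 and an adult T-score SD of 10, effects of 0.6 × 8 = 4.8 raw points and 0.6 × 10 = 6.0 T-score points average to 5.4, which is neither.

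**3. Power for the planned contrast, change from baseline to week 8.** A constant difference between the two scales cancels within each person. With ρ = 0.5 the change has variance factor 2(1 − ρ) = 1.
- Common metric: z = 0.6 × 3.873 − 1.96 = 0.36, so 64% (about 62–63% by t and in simulation).
- Mixed metrics, simulated: about 61% at k = 0.8 and about 58% at k = 0.5.

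**4. Power for a contrast of levels, no age term.** Here the gap between the two scales enters the error. Simulated power for the averaged difference (20,000 runs, all values of k and adult share above):

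| Gap between scale means | Power |
|---|---|
| common metric | about 75% |
| mixed, 0 points | 70–76% |
| mixed, 10 points | 56–66% |
| mixed, 20 points | 17–40% |
| mixed, 40 points | 0–2% |

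The larger gaps are not far-fetched. An adult who enters through fatigue has a T-score of at least 60, and no adolescent raw score exceeds 40, so the baseline gap from such an adult is at least 60 − 40 = 20 points. Participants who enter through depression or pain may narrow it.

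**5. What drives the level-based loss.** With means of 22 and 62, SDs of 8 and 10, and equal age groups (all assumed), ANCOVA power is:
- T-scores, no age term: 74.4%
- mixed metric with an age term: 73.8%
- mixed metric, no age term: 64.7%

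A week-8 comparison of levels on the mixed metric with an age term has 62.5%, against 63.1% on a common metric. The missing age term accounts for nearly all of the loss.

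**The case against.** The best reply is that T-scores are already the working metric. The entry rules for both symptoms are in T-scores without an age limit, so adolescent scores must be converted at screening, and the 0–40 and 0–56 ranges may only describe the forms. The article is also a condensed account, and a fuller analysis plan may name the metric and the covariates. This stands in part: the harm is conditional on a scoring choice that the text leaves open. It does not remove the point, because the article sets out scoring for each form and attaches conversion to one fatigue form only.

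Three stronger readings are tempting and not supported.

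- **That the fatigue cut-off cannot be applied to adolescents.** A raw score of 40 cannot reach 60, but this shows that adolescent T-scores must exist at screening, not that they are lacking.
- **That pooling would destroy the trial's power.** The near-zero figures belong to contrasts of levels without an age term. The Statistical analysis plan section names change from baseline, where the loss is a few points. ANCOVA is not planned, and its loss comes from the missing age term rather than from the mixed metric.
- **That participants who turn 18 would switch forms.** The article does not say so. If ages are spread evenly over 11 years, about 75/11 × 8/52 = 1 participant of 75 would turn 18 by week 8.

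**Conclusion.** The point holds as a defect of specification. The article describes age-specific instruments on different metrics, analyses one mean change per symptom over both age groups, and does not say which metric is analysed. If followed literally, the main secondary estimate has no single unit and gives adolescents less than their share whenever their raw SD is below the adult T-score SD: about 33% instead of 50% at an SD ratio of 0.5.

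For the planned change from baseline the cost in power is small, about 62% down to 58–61%. It becomes large only for contrasts of levels without an age term, which include the averaged difference named in the Sample Size Estimate. The SD ratio, the gap between scales, the age mix and the correlation are assumptions. The matter concerns secondary outcomes of a feasibility pilot, so it should be put right but does not threaten the trial's primary aim.

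**What to change.** 1. In the Fatigue, Depressive symptoms and Statistical analysis plan sections, state that both fatigue forms and both depression inventories are analysed as T-scores, or alternatively as change standardized within instrument.
2. Include the randomization age group in the repeated measures model, together with its interaction with time.
3. Acknowledge that T-scores from different instruments, the CDI-II and BDI-II above all, are not strictly equivalent.

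Showing effects by age group beside the pooled one is optional and, with about 60 completers, descriptive only.

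The cost is scoring and wording. No new data are needed, since T-scores are already required for eligibility and age group is already recorded as a stratum. The remaining limit is the one in item 3: a shared metric makes the pooled change readable but does not make two instruments the same.

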#### Depressive symptoms

*The Children’s Depression Inventory 2nd Edition (CDI-II)* and *The Beck Depression Inventory-II (BDI-II)* assess depressive symptoms in the past two weeks for children and adults, respectively [22, 23]. The CDI-II consists of 28 items scored 0–2 for a total score 0–56. The BDI-II is a 21-item measure (scores 0–3) for a score 0–63, which can be transformed into a T-score. Higher scores on these measures indicate more severe symptoms. T-scores of ≥ 60 and ≤ 90 indicate eligibility.

#### Pain intensity

Average pain intensity over the past two weeks will be assessed using a *Visual Analog Scale (VAS),* a well-utilized measure of pain intensity [24, 25]. Values range from 0 (*no pain)* to 10 *(worst imaginable pain)* with a rating of ≥ 3 used [26] to indicate eligibility.

### Demographics

#### Demographic information

Age, sex, race, ethnicity, disease duration, family income, and caregiver occupation will be obtained. Caregivers will provide this information for adolescent participants. Information on the participant’s occupation, education, and residence will also be explored for those over age 18.

### Additional outcomes

#### Health-related outcomes

##### Disease activity & damage

Disease activity will be recorded by study rheumatologists via the *Systemic Lupus Erythematosus Disease Activity Index (SLEDAI-2 K)* [27] and the *Systemic Lupus International Collaborating Clinics Damage Index (SDI)* [28]. Scores on the SLEDAI-2 K range from 0 *(no activity)* to 105, with higher scores indicating greater disease activity, and scores on the SDI range 0–47, with higher scores indicating greater disease damage.

##### Medication use

Will be obtained via self/parent-report.

##### Medication adherence

Will be obtained through the *Medication Adherence Self-Report Inventory (MASRI)* [29], which consists of six items to measure missed medications.

##### Health-related quality of life

The *PedsQL Quality of Life Inventory *[30]* and PedsQL Rheumatology Module *[31] will assess participant quality of life. Participants under the age of 18 and their caregivers complete these measures. Items are scored on a 5-point Likert scale (*0* = *Never, 4* = *Almost Always).*

##### Pain interference

The *PROMIS Pain Interference Pediatric *[32, 33] *and Adult Form v1.0 Short Form *[34] will assess pain interference. The measure consists of eight questions on a 5-point Likert Scale ranging from 1 *(Not at all)* to 5 *(Very Much)*. A higher score represents higher pain inference in daily functioning.

### Mental health-related outcomes

#### Anxiety

The *Screen for Child Anxiety Related Disorders (SCARED)* is a self-report measure that assesses anxiety over the past three months [35]. Items include a 3-point Likert scale (*0* = *not true or hardly ever true, 2* = *very true or often true*) and totals range from 0–82. A score ≥ 25 indicates clinically significant anxiety.

#### Resilience

Will be measured using the *Brief Resilience Scale *[36]*,* a six item measure scored a 5-point Likert scale ranging from 1 = *Strongly disagree* to 5 = *Strongly Agree*. Items are averaged to create total possible scores 1–5, with higher scores indicating stronger resilience.

#### Adverse Childhood Experiences (ACEs)

*Adverse Childhood Experiences (ACEs)* is a nine-item form to assesses adverse events such as discrimination and violence experienced prior to age 18 [37]. It is completed directly by participants ages 18 years or older, or by caregivers for those under 18 years of age. Scores range 0-9, with higher scores indicating higher risk for adversities.

#### COVID-19-related distress

Participants will evaluate their average level of COVID-related distress *(0* = *no distress to 100* = *extreme distress)*, and (if appropriate) 2) the degree to which TEACH helped them cope with this distress *(0* = *not at all to 100* = *very much)*. COVID-related distress will be measured at each assessment point, whereas coping will only be administered after the TEACH program is completed. We created this measure for use in the study and it is comparable with how COVID-distress is measured using other approaches {Kazak, 2021 #174}.

#### Caregiver mental health

The *Depression Anxiety Stress Scales-21 (DASS-21) *[38] is a self-report measure that will assess caregiver mental health. The DASS-21 consists of 21 items that assess depression, stress, and anxiety. Items are rated from 0 *(Did not apply to me at all)* to 4 *(Applied to me very much, or most of the time),* with higher scores indicating more mental health symptoms.

### Daily diaries

Daily diaries will be completed by participants during the TEACH program to assess pain, mood, and fatigue. Each domain is assessed on a VAS, with qualitative end anchors (e.g., Pain = *No pain* to *Worst possible pain*; Mood = *Great* to *The worst;* Fatigue = *Not tired at all* to *Extremely tired)*.

### Adverse events

The Negative Effects Questionnaire, a 20-item questionnaire to examine adverse/unwanted events experienced during TEACH [39]. Participants will indicate whether they experienced the event and if it was related to TEACH. The degree of negativity is also measured on a 4-point Likert scale ranging from minimum to maximum.

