### Study procedures

Physicians will identify youth who meet criteria for cSLE, introduce the study, and then study staff will speak with the family to obtain consent/assent. If study staff are not physically present, virtual consent procedures will be conducted via phone and REDCap’s eConsent Framework to minimize patient risk. After consent, study staff will conduct a psychosocial screening to determine eligibility (~ 5 min), as well as a baseline assessment with qualifying youth (see Fig. 1). Eligible patients will then be randomized to receive TEACH + TAU or TAU alone (See Fig. 2). Approximately eight and 20 weeks later, all subjects will be re-assessed on study outcomes. If significant symptom levels remain (or if family requests additional care), participants will be offered appropriate referrals. Following the post assessment, those randomized to TAU will then be eligible to receive TEACH+TAU (see Fig. 2). Subjects will receive up to $100 in Amazon gift cards ($50 at baseline and $50 at the eight-week assessment; no compensation is offered for 20-week assessment). Participants at the CAN site will receive research volunteer hours at the 20-week visit.

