### Randomization and blinding

Eligible participants will be randomized to receive either TEACH + TAU or TAU alone in this open trial. Randomization scheduling will be computer-generated by a biostatistician at MSU and stratified based on the two main study sites and two age groups (< 18, 18 +), with a 1:1 ratio for each condition. We will also use blocking to keep the ratio of TEACH + TAU vs. TAU approximately equal throughout the trial. The study team including the site recruiters will be masked to the block size(s). Post assessment and follow up measures will be collected autonomously using online methods, allowing for blinded collection of outcome data irrespective of group assignment.

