## Discussion

cSLE is a chronic, debilitating autoimmune disease associated with more severe symptoms as compared to adult-onset SLE and a 20-fold increased risk of mortality [49]. cSLE is commonly associated with fatigue, mood issues, and pain, which contribute to poor health-related quality of life [2, 3]. Given these common symptoms are modifiable with nonpharmacological therapies, CBT may optimize patient outcomes as part of a multi-disciplinary approach to care [50]; however, there is mixed evidence to date that CBT manages mood and related symptoms in children [18, 51] and adults [13] with SLE. A tailored intervention such as TEACH using evidence-based cognitive behavioral and mindfulness meditation techniques to manage fatigue, depressive symptoms and pain may be needed to address concerns specific to this population.

While we have demonstrated feasibility of TEACH in a pilot investigation [18], a rigorous and well-controlled trial of this promising approach is critically needed to advance understanding and improve outcomes for youth with cSLE. TEACH is a brief tailored therapy designed to improve fatigue, mood, and pain in youth with cSLE. It is important to assess if TEACH is feasible and associated with improvements in these symptoms following treatment as compared to standard medical care. Once these effects are established, we will investigate additional factors such as patterns/predictors of treatment response.

COVID-19 impacted the study planning and recruitment plan. As such, COVID-related distress will now be measured and targeted. Furthermore, we expect enrollment rates to vary during different periods of the COVID-19 pandemic. We will examine these data carefully in the context of when it was collected.

We anticipate minimal risk and maximal benefits to patients/families. The present trial allows for understanding of treatment effects. Lack of active treatment comparator and a modest sample size are limitations. In the future, we plan to test the *implementation* of TEACH in a larger scale multi-site investigation and assess sustainability of treatment effects. Assuming TEACH is effective and future implementation efforts are successful, we will share the program with rheumatology providers to integrate TEACH into routine care. Future work will also examine mechanisms of treatment response and whether modifications (e.g., booster sessions) are needed.

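### The one adverse-event instrument described covers only time in TEACH and relies on unblinded self-attribution, so event reports have no concurrent TAU comparator in the randomised eight weeks

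*Protocol article*

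**What the plan says.** The Adverse events section consists of a short description of the Negative Effects Questionnaire: "a 20-item questionnaire to examine adverse/unwanted events experienced during TEACH". On attribution it says: "Participants will indicate whether they experienced the event and if it was related to TEACH". A four-point rating of how negative each event was is also taken.

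Under Randomization and blinding: "Eligible participants will be randomized to receive either TEACH + TAU or TAU alone in this open trial", "with a 1:1 ratio for each condition". Under Study procedures: "Following the post assessment, those randomized to TAU will then be eligible to receive TEACH+TAU".

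Other measures are not limited to one arm. Study procedures also says: "Approximately eight and 20 weeks later, all subjects will be re-assessed on study outcomes". The outcome sections list fatigue, depressive symptoms and pain, and add rheumatologist-recorded disease activity, anxiety and COVID-related distress. The Statistical analysis plan section analyses mean change in the three symptom outcomes from baseline to week 8 against the control group. The rest is left to exploratory work. The Discussion says: "We anticipate minimal risk and maximal benefits to patients/families".

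**The concern.** The instrument is defined by exposure to TEACH. A TAU participant has no TEACH period to report on until the post assessment is over, and by then the randomised comparison has ended. Later TAU answers would come from people who have received TEACH and would also lack a control.

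Within TEACH, the only means of separating an effect of the programme from background is the participant's own opinion, given with knowledge of the assigned arm. Background will not be negligible. Eligibility requires elevated fatigue, depressive symptoms or pain, and the depression ceiling was raised from T 80 to T 90 in August 2021 because symptoms had increased during the pandemic. Unwanted experiences will occur without TEACH, and self-attribution can err in either direction.

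What is at stake is the expectation of minimal risk. A randomised design could describe it against a control, but the named instrument collects events as a single-arm study would.

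**Working it through.** **1. Who can report events, and when**

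| Period | TEACH + TAU | TAU alone |
|---|---|---|
| Baseline to week 8 (randomised) | Event questionnaire; symptom and disease scores | Symptom and disease scores; no event questionnaire described |
| After week 8 | Scores at week 20 | May enter TEACH; any event questionnaire then is uncontrolled |

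The daily diaries are likewise tied to the TEACH programme, so they supply no TAU comparator either.

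**2. Numbers per arm**

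The Sample Size Estimate gives 60 completers and 80% retention: 60/0.80 = 75, which reproduces the stated enrolment. At 1:1 this is 37 or 38 randomised and 30 completers per arm. The article gives no event rate, so every rate below is an assumption.

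**3. What a single-arm count can show**

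- Expected TEACH reports if TEACH has no effect: 37 × 0.10 = 3.7, or 37 × 0.20 = 7.4.
- Suppose 8 of 38 report an event: 21.1%, exact (Clopper-Pearson) 95% interval 9.6% to 37.3%. Against a 10% background this is an excess of 11 points; against 30% it is a deficit of 9 points. Without a TAU count nothing but self-attribution distinguishes the two.
- Zero events still allow a true rate of up to 1 − 0.05^(1/38) = 7.6% (one-sided 95%), or 1 − 0.05^(1/30) = 9.5% with 30 completers.

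**4. What collection in both arms would add**

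It supplies the missing estimate, but an imprecise one. Continuing the example, with difference ± 1.96 × √[p₁(1−p₁)/n + p₂(1−p₂)/n]:

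- 8/38 v 4/38: +10.5 points (−5.7 to +26.8), Fisher p = 0.35.
- 8/38 v 11/38: −7.9 points (−27.3 to +11.5), Fisher p = 0.60.

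If the two observed rates were equal, the largest excess not excluded is 1.96 × √[2p(1−p)/n]:

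| Observed rate in both arms | n = 30 per arm | n = 38 per arm |
|---|---|---|
| 10% | 15.2 points | 13.5 points |
| 20% | 20.2 points | 18.0 points |

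As a test (two-sided 5%, normal approximation), 80% power needs the following TEACH rates:

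| Assumed TAU rate | 30 per arm | 37 per arm |
|---|---|---|
| 5% | about 33% | about 30% |
| 10% | about 41% | about 38% |
| 20% | about 55% | about 51% |

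Power for 10% v 20% is 19% with 30 per arm and 22% with 37.

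**The case against.** The strongest reply is that harm is already measured in both arms. Everyone is re-assessed at about 8 and 20 weeks. Low mood, pain, fatigue, anxiety, COVID-related distress and disease activity are all scored, and no participant attribution enters those scores. The fatigue sample size rests on a two-sided test, so average worsening under TEACH would show. This stands. A reader might infer from the Adverse events section that TAU has no harms data at all and that the trial cannot tell whether TEACH causes harm; the both-arm scores rule that reading out.

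A second reply is that the document is a condensed article. It does not say that this questionnaire is the only harms collection, and general or serious adverse-event reporting may sit in the full protocol. The Eligibility criteria section also describes a response to safety concerns that is not restricted by arm. This stands too, and the point does not rest on any such absence. It rests on what the article states: the instrument, its scope and who attributes cause.

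Third, this is a pilot with feasibility as its primary outcome and no harms hypothesis, and both-arm collection could not separate the scenarios in the example either. That is correct, and it limits the claim to description. It does not remove the value of a concurrent count, because a wide interval around a randomised difference is more informative than a rate with nothing to compare it to.

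Finally, the questionnaire's items are not reproduced in the article, so some may make no sense to a person who has had no therapy. The fix has to allow for that.

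**Conclusion.** The point holds in a limited form. On the plan as described, adverse-event reports have no concurrent TAU comparator during the randomised eight weeks, and relatedness rests on the opinion of unblinded participants. The symptom scores partly fill the gap, but they are described only as efficacy or exploratory outcomes and chiefly as mean change, which can conceal a minority who deteriorate.

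The size cannot be taken from the document. With assumed background rates of 10% to 20%, roughly 4 to 7 of 37 TEACH participants would report events with no effect of TEACH. It would be wrong to conclude that the trial is blind to harm, or that collecting events in both arms would turn it into a safety test. This is a worthwhile, inexpensive improvement and not a flaw that undermines the trial's feasibility aim.

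**What to change.** 1. **By-arm worsening table.** Report by randomised arm the number of participants whose fatigue, depressive symptoms or pain worsened from baseline to week 8 by an amount stated in advance for each measure. Show those with no week-8 score as a separate row, since about 75 − 60 = 15 participants are expected to be missing. This uses data already collected and costs one table.
2. **A common event list at week 8.** At the online assessment already scheduled, ask both arms the questionnaire's event and severity items that do not presuppose therapy. Keep therapy-specific and relatedness items for TEACH only. Which items fall in each group has to be settled with the instrument in hand. Present event counts by randomised arm with confidence intervals for the difference, labelled as descriptive.

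The cost of the second change is a few minutes of burden for TAU participants and a short addition to an existing form. It helps only those who have not yet passed week 8, whereas the first change can be made at any time before analysis. Neither alters treatment, sample size or visit schedule.
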